## Abstract

Long-term sequelae refer to persistent symptoms or signs for >6 months after SARS-CoV-2 infection. The most common symptoms of sequelae are fatigue and neuropsychiatric symptoms (concentration difficulty, amnesia, cognitive dysfunction, anxiety, and depression). However, approved treatments have not been fully established. Herbal medicines are administered for 12 weeks to patients who continuously complain of fatigue or cognitive dysfunction for >4 weeks that only occurred after COVID-19 diagnoses. Based on the Korean Medicine syndrome differentiation diagnosis, patients with fatigue will be administered Bojungikgi-tang or Kyungok-go, whereas those with cognitive dysfunction will be administered Cheonwangbosim-dan. Results could support evidence that herbal medicines may mitigate fatigue and cognitive dysfunction caused by COVID-19. Furthermore, by investigating the effects of herbal medicines on changes in metabolite and immune response due to COVID-19, which may be responsible for sequelae, the potential of herbal medicines as one of the therapeutic interventions for post-acute sequelae of SARS-CoV-2 infection can be evaluated. Therefore, the effects of herbal medicine on fatigue and cognitive dysfunction sequelae due to COVID-19 will be elucidated in this study to provide an insight into the preparation of medical management for the post-acute sequelae of SARS-CoV-2 infection.

## 1. Introduction

Due to the global Coronavirus Disease 2019 (COVID-19) pandemic, medical and research capabilities have concentrated on the development of vaccines for the prevention of infectious diseases, blocking the spread of infection, and treatment of acute infectious conditions. However, life-threatening acute infections, including post-acute sequelae of SARS-CoV-2 infection, have been widely reported. A recent study on the follow-up observation of 1250 patients with severe COVID-19 who were hospitalized in 38 hospitals in Michigan, USA, reported that many COVID-19 survivors were unable to perform their normal activities due to various physical and mental sequelae after discharge. They reported difficulties in performing activities of daily life that lead to reduced working hours or complete unemployment [1]. Symptom management after a complete recovery from acute SARS-CoV-2 infection currently requires attention.

Fatigue is the most frequently reported symptom among the COVID-19 sequelae. More than half of survivors had fatigue for at least 6 weeks; however, the relationship between severity of acute COVID-19 and fatigue has not been confirmed, which might suggest that even survivors of mild COVID-19 can experience fatigue that lasts for a considerable time. Notably, more than half of those who have recovered from COVID-19 complain of fatigue regardless of symptom severity [2]. Further, cognitive dysfunction, also known as “brain fog”, is reported in a large number of patients who have recovered from COVID-19. Researchers at Imperial College London reported in an intelligence test they conducted that 84,285 people who had recovered from COVID-19 showed lower cognitive abilities than those who were not infected. In particular, it was reported that the more severe the COVID-19 symptoms, the greater the sequelae, and brain clouding also occurred in participants who had recovered for several months. Those who had recovered from COVID-19 scored lower verbal ability, logical ability, spatial perception ability, concentration, and emotional regulation ability than non-infected people, and the brain age of patients who were treated in an intensive care unit or used a ventilator, was at the maximum. Such forgetfulness (decrease in cognitive ability) decreased daily life and work ability, and was commonly experienced by patients with severe symptoms in the acute stage as well as recovered patients who had experienced milder symptoms and who had not received inpatient treatment [3].

As for these sequelae of COVID-19, accurate identification of pathological mechanisms of each symptom is an urgent medical problem; nonetheless, an appropriate treatment strategy is not yet established [4]. In this context, we will try to access the potential effects of widely used herbal medications for patients with fatigue and cognitive dysfunction after recovering from COVID-19, and to test the feasibility of this clinical study design for future clinical trials with sufficient sample size on these symptoms in the future.

## 2. Methods

### 2.1. Objectives

This study is a phase 2 preliminary clinical trial to evaluate the safety and effectiveness of commercially available herbal medicines for fatigue or cognitive dysfunction after recovering from COVID-19. It also aims to provide basic evidence for future large-scale clinical trials by evaluating the feasibility of the study design and interventions. The primary objective is to investigate the effects of 12-week herbal medication on the treatment success rate in patients with fatigue or cognitive dysfunction after recovering from acute COVID-19 infection. The secondary objective is to evaluate the feasibility of the study design, such as patient recruitment rate and dropout rate during the trial. Moreover, the effects of herbal medicines on immune responses related to COVID-19 and on metabolites related to fatigue and cognitive dysfunction will be assessed.

### 2.2. Study Design

Written informed consent will be obtained from all patients before participating in this study. We will recruit patients with fatigue or cognitive symptoms and three Korean Medicine (KM) herbal medications will be prescribed to each patient based on the syndrome differentiation based on the symptom type. Patients will visit once per month during a 12-week medication period and then will visit for the examination of symptoms, a blood chemistry check, and immunological tests every 12 weeks over 24 weeks. The flow diagram and study schedule are shown in Figure 1 and Table 1.

### 2.3. Sample Size

The current study is a phase 2 preliminary clinical study, thus we will recruit 45 patients without sample size calculations. Fifteen patients will be assigned to each of the three intervention groups. The results from this study will be used to calculate the sample size for further confirmatory clinical trials.

### 2.4. Participants

#### 2.4.1. Inclusion Criteria

The inclusion criteria are as follows:Those aged >19 years and have been diagnosed with COVID-19 and recovered. To confirm the COVID-19 diagnosis and recovery, medical history will be examined by reviewing the submitted medical records about the diagnosis, hospitalization, and certificate of SARS-CoV-2 negative or conduct COVID-19 antibody test using the COVID-19 IgM/IgG Plus Test kit (Sugentech, Inc., Daejeon, Korea) approved by the Korean Ministry of Food and Drug Safety. If submission of medical records is possible, the antibody test can be skipped.Those who are continuously complaining of fatigue or cognitive dysfunction for >4 weeks that they did not experience before their COVID-19 diagnosis.Those who scored a total of >76 points on the Checklist Individual Strength (CIS).Participants do not have any problems with overall cognitive function and must be capable of providing written informed consent to participate in the study.

#### 2.4.2. Exclusion Criteria

The following exclusion criteria are considered:Those who have been diagnosed with diseases that can cause fatigue (cancer, sleep disturbance, chronic hepatitis, liver cirrhosis, chronic renal failure, tuberculosis, asthma, multiple sclerosis).Those who have been diagnosed with diseases that can cause brain fog (cerebral hemorrhage, cerebral infarction, brain tumor, Parkinson’s disease, epilepsy, major depressive disorder, bipolar affective disorder, schizophrenia, delusional disorder, or dementia).Those who have medical problems that may affect the intake or absorption of drugs (dysphagia, clinically serious digestive disorders, galactose intolerance, Lapp lactase deficiency, or glucose-galactose malabsorption).Those currently with or have a medical history of allergy to clinical trial drugs (herbal medicines).Those who have been diagnosed with liver or kidney disease, or have abnormal levels in blood tests (exceed 3 times the upper limit of normal aspartate aminotransferase (AST), alanine aminotransferase (ALT), blood urine nitrogen (BUN), or creatinine level).Pregnant, lactating, and fertile women who have a pregnancy plan.Those who have participated in other clinical trials within 30 days of participating in this study.Those who are judged to be inappropriate for the clinical trial by the researchers due to clinically significant psychiatric symptoms, physical conditions, laboratory findings or other medical states.

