#### 2.4.3. Withdrawal and Discontinuation Criteria

The reasons for withdrawal and discontinuing herbal medication or observation shall be documented. The patients’ withdrawal criteria are as follows:Acute reaction (allergy, hypersensitivity, and others) to herbal medicine.A violation of the inclusion/exclusion criteria is confirmed during the trial.No longer possible to administer or make observations due to unexpected diseases or accidents.No longer possible to administer or make observations due to severe adverse events or adverse drug reaction.The patient is pregnant.Withdrawal of consent by patients or their agents.It is judged by researchers that the trial is difficult to continue.

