### 2.9. Safety Evaluation

For safety evaluation, adverse events, vital signs, laboratory tests, and electrocardiograms will be evaluated. Adverse events refer to all harmful and unintended symptoms or signs, including abnormal results in laboratory tests, or diseases that occurred in patients administered herbal medicine that do not necessarily have to be a causal relationship. Vital signs including blood pressure, body temperature, breathing, and heart rate, will be recorded at every visit. Electrocardiography will be performed to monitor the presence of severe heart disease, such as acute myocardial infarction and ventricular fibrillation. Laboratory tests will determine the red blood cell, hemoglobin, hematocrit, platelet, white blood cell, fasting blood sugar, BUN, creatinine, AST, ALT, and blood electrolyte (Na, K, Cl) levels, and the observed values and changes from the baseline value will be evaluated.

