## Figures and Tables

**Figure 1 healthcare-10-01839-f001:**
[figure not shown]
Flow diagram and schedule.

**Table 1 healthcare-10-01839-t001:** Schedule summary.

Visit	0	1	2	3	4	5	6	UV *
Week	−7	1	5	9	13	25	37	-
Visit Window	-	2	±7	±7	±7	±7	±7	-
Informed consent for the study	●							
Demographic information	●							
Participation in other clinical trials	●							
Medical history	●							
Confirmation of diagnosis of COVID-19 infection	●							
Medication history	●							
Vital signs	●	●	●	●	●	●	●	●
Electrocardiogram	●				●			●
Laboratory test	●				●			●
Blood collection for immune response and metabolite analysis	●				●	●	●	●
Pregnancy **	●							
Evaluation of fatigue or brain fog	●							
CIS	●		●	●	●	●	●	●
VAS (0–100) score for fatigue or brain fog	●		●	●	●	●	●	●
Inclusion/exclusion criteria	●							
KM syndrome differentiation		●						
Prescription of herbal medicine ***		●	○	○				
Drug adherence			●	●	●			●
Check for combination therapy			●	●	●	●	●	●
ChFQ		●	●	●	●	●	●	●
EQ-5D-5L		●	●	●	●	●	●	●
PSQI-K		●	●	●	●	●	●	●
K-MoCA		●	●	●	●	●	●	●
CFQ		●					●	●
BDI		●	●	●	●	●	●	●
Digit span test in K-WAIS (DF, DB, and DF-DB)		●			●	●	●	
K-BNT-15		●			●	●	●	
Adverse events check		●	●	●	●	●	●	●

●, check on visit; ○, if applicable * UV, unscheduled visit (), ** only fertile women, *** Evaluation for the continuation of herbal medicine administration at 5th and 9th weeks.

**Table 2 healthcare-10-01839-t002:** KM syndrome differentiation for allocation to treatment group.

	Fatigue		Cognitive Dysfunction
Code	CV1	CV2	CV3
Syndrome differentiation classification	Spleen-lung qi deficiency pattern	Dual deficiency of qi and yin pattern	Heart yin deficiency heat pattern
Symptom	Fatigue, appetite loss, cold sweat, shortness of breath, chest tightness, anxiety and others	Fatigue, dry cough and others	Forgetfulness, fever, insomnia, heart palpitation, stomatitis, tongue needles and others
Tongue diagnosis	Pale tongue, thin white fur	Dry mouth, dry tongue	Red tongue and low tongue coated
Pulse diagnosis	Vacuous, large, weak pulse/surging, large pulse	Fine pulse/vacuous, weak pulse	Fine, rapid pulse
Urine/feces	Difficult stool to pass/sloppy stool	Dry stool	Inhibited stool/sloppy stool

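### The creatinine exclusion (above 3 x ULN, the multiple used for AST and ALT) lets through an eGFR of about 14 to 26, so it does not screen out undiagnosed severe renal impairment

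*Protocol article*

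**What the plan says.** Section 2.4.2 joins a diagnosis limb and a laboratory limb in one criterion: "Those who have been diagnosed with liver or kidney disease, or have abnormal levels in blood tests". The laboratory limb is then given as a number: "exceed 3 times the upper limit of normal aspartate aminotransferase (AST), alanine aminotransferase (ALT), blood urine nitrogen (BUN), or creatinine level". The listed criteria contain no eGFR or creatinine-clearance limit.

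Three other parts of section 2.4.2 bear on renal function:

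- The first exclusion, for diagnosed causes of fatigue, includes "chronic hepatitis, liver cirrhosis, chronic renal failure".
- BUN has its own limit, at the same multiple.
- The last exclusion covers people "judged to be inappropriate for the clinical trial by the researchers due to clinically significant psychiatric symptoms, physical conditions, laboratory findings", with no threshold attached.

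Section 2.9 lists the safety laboratory panel, including "fasting blood sugar, BUN, creatinine, AST, ALT, and blood electrolyte (Na, K, Cl) levels". Table 1 schedules the laboratory test at visit 0, at visit 4 (week 13) and at unscheduled visits. Medication is first prescribed at visit 1.

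**The concern.** A given multiple of ULN does not mean the same thing for a transaminase as for creatinine. Creatinine varies roughly inversely with filtration, so a threefold rise means that most filtration has been lost. The protocol evidently wants renal disease out of the trial: it excludes diagnosed kidney disease whatever its degree, and it names chronic renal failure among the causes of fatigue. For a patient without a diagnosis, the laboratory limb is the only objective screen, and at 3 x ULN it passes values in the severe range.

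Two things are at stake, both modest.

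- **Safety and consistency.** Whether such a patient is enrolled depends on case-by-case judgement instead of a written rule. Once enrolled, the patient has no scheduled laboratory test until visit 4, after up to 12 weeks of medication.
- **Attribution.** Fatigue with a renal contribution could be counted as a COVID-19 sequela. Section 2.4.1 requires the symptoms to be new since COVID-19, which narrows this route without closing it.

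**Working it through.** The protocol article states no eGFR, so there is no figure of its own to reproduce. The check converts its creatinine limit to eGFR.

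**Inputs from the document:** the limit of 3 x ULN (section 2.4.2), and age above 19 with no upper limit listed (section 2.4.1).

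**Assumptions, not in the document:** creatinine ULN 1.1 to 1.3 mg/dL in men and 0.9 to 1.1 in women, with wider values as a sensitivity check; ages 20 to 75; BUN ULN 20 to 23 mg/dL; eGFR below 30 taken as severe impairment.

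**Formula (CKD-EPI 2021).** For creatinine (Scr) above k, which holds throughout here:

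eGFR = 142 x (Scr/k)^-1.200 x 0.9938^age, times 1.012 in women; k = 0.9 (men), 0.7 (women).

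**Step 1: eGFR at creatinine 3 x ULN**

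Worked case, man aged 50, ULN 1.2: Scr = 3.6; (3.6/0.9)^-1.2 = 0.1895; 0.9938^50 = 0.7327; 142 x 0.1895 x 0.7327 = 19.7.

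| Sex | ULN | 3 x ULN (mg/dL) | Age | eGFR |
|---|---|---|---|---|
| Men | 1.1 | 3.3 | 20 | 26.4 |
| Men | 1.2 | 3.6 | 50 | 19.7 |
| Men | 1.3 | 3.9 | 75 | 15.3 |
| Women | 0.9 | 2.7 | 20 | 25.1 |
| Women | 1.0 | 3.0 | 50 | 18.4 |
| Women | 1.1 | 3.3 | 75 | 14.0 |

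**Step 2: sensitivity**

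- Higher ULNs (1.4 men, 1.2 women) at age 75 give 14.0 and 12.6.
- A low female ULN of 0.8 at age 20 gives 28.9.
- Over ages 20 to 80 with the base ULNs, CKD-EPI 2009 gives 12.6 to 25.5 and MDRD gives 13.5 to 24.0. With the wider ULNs the lowest value from any equation is 11.3.

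No combination reaches 30.

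**Step 3: creatinine at eGFR 30**

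Solving the formula for creatinine: Scr = k x (142 x 0.9938^age x sex factor / 30)^(1/1.2), with sex factor 1 in men and 1.012 in women.

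| Sex | Age 20 | Age 50 | Age 75 | As multiple of ULN, ages 20 to 75 |
|---|---|---|---|---|
| Men | 2.96 | 2.54 | 2.23 | 1.71 to 2.69 |
| Women | 2.33 | 1.99 | 1.75 | 1.59 to 2.59 |

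Every multiple is below 3, so an eGFR limit of 30 is stricter than the current limit throughout. Every multiple is also well above 1, so a normal creatinine does not fail it.

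**Step 4: does the BUN limit cover the gap?**

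The BUN limit is 3 x 20 = 60 to 3 x 23 = 69 mg/dL. The BUN:creatinine ratio needed to reach it is:

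- at eGFR 30, age 50: 60/2.54 to 69/2.54 = 23.6 to 27.2 (man); 60/1.99 to 69/1.99 = 30.2 to 34.7 (woman);
- at creatinine 3 x ULN: 60/3.6 to 69/3.6 = 16.7 to 19.2 (man, ULN 1.2); 60/3.0 to 69/3.0 = 20.0 to 23.0 (woman, ULN 1.0).

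The BUN limit may or may not be met, so it cannot be relied on to close the gap.

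**The case against.** The strongest reply is that this is a preferred cut-off, not a defect, because other routes already cover the patient in question. Diagnosed kidney disease and chronic renal failure are excluded, BUN has a limit, and the researchers may exclude on laboratory findings. The visit 0 result is available before the visit 1 prescription. For the number to matter, a patient needs raised creatinine, no prior diagnosis, BUN under its limit, and a physician who sees the result and does not act. This stands as a statement about probability, and it is why the point is minor. It does not repair the number: one safeguard needs a prior diagnosis, one is similarly loose, and one has no threshold.

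A second reply is that the cut-off of 30 comes from outside the document, which gives no renal dosing or toxicity data, and that eGFR 30 to 59 would still pass the number. That is correct. The value 30 is offered as a floor, and the sponsor's clinicians may set it higher.

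A third reply concerns monitoring. Patients are seen at visits 2 and 3, with adverse events and vital signs checked, and unscheduled visits include laboratory tests. That is also correct. Nor does the withdrawal rule ("A violation of the inclusion/exclusion criteria is confirmed during the trial") add much to the concern: a patient under 3 x ULN violates no numeric limit, and no scheduled laboratory result before visit 4 could reveal a later breach. The missing mid-treatment test only means that more depends on screening.

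Finally, the article condenses a fuller protocol, which may say how abnormal screening values are handled. The threshold itself, however, is stated here.

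**Conclusion.** The concern holds in its narrow form. The numeric creatinine limit does not exclude undiagnosed severe renal impairment: just under it, eGFR is about 14 to 26 on the base assumptions and below 30 in every variant tried. The ULNs, ages and equations are assumptions, but the conclusion did not change with any of them. The exclusion criteria are alternatives and do not contradict one another; the creatinine number is simply too high to do this job by itself. The document gives no frequency of undiagnosed renal impairment, few if any of the 45 patients are likely to be affected, and no harm from the three medicines is claimed. This is an optional improvement, held with medium confidence.

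**What to change.** In section 2.4.2, keep the 3 x ULN limit for AST, ALT and BUN. Replace the creatinine multiple with exclusion at eGFR below 30 mL/min/1.73 m2 (CKD-EPI 2021), calculated from the visit 0 creatinine. At age 50 this is a creatinine of about 2.54 mg/dL in men and 1.99 mg/dL in women. The sponsor's clinicians may choose a stricter value; nothing here requires 60. Keep the laboratory-findings exclusion for results inside the limits.

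The cost is one line of text and a calculation on a test already done. The downside is a rare extra screening failure. Older patients with normal creatinine are not lost: at age 75 the limit is still 1.71 to 2.03 x ULN in men (2.23/1.3 to 2.23/1.1) and 1.59 to 1.95 x ULN in women (1.75/1.1 to 1.75/0.9, from unrounded creatinine).

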#### 2.4.3. Withdrawal and Discontinuation Criteria

The reasons for withdrawal and discontinuing herbal medication or observation shall be documented. The patients’ withdrawal criteria are as follows:Acute reaction (allergy, hypersensitivity, and others) to herbal medicine.A violation of the inclusion/exclusion criteria is confirmed during the trial.No longer possible to administer or make observations due to unexpected diseases or accidents.No longer possible to administer or make observations due to severe adverse events or adverse drug reaction.The patient is pregnant.Withdrawal of consent by patients or their agents.It is judged by researchers that the trial is difficult to continue.

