### 2.7. Intervention

Based on the syndrome differentiation diagnosis, three different herbal medications will be prescribed to each patient for up to 12 weeks. Among the patients with fatigue, the pattern/syndrome of lung-spleen qi deficiency group will be administered Bojungikgi-tang (CV1, Kracie Bojungikgitang Extract Fine Granule, Kolmar Pharma, Korea), and the syndrome of dual deficiency of qi and yin group will be administered Kyungok-go (CV2, Kyungbang Kyungokgo, KBPharm, Korea). The cognitive dysfunction group will be administered Cheonwangbosim-dan (CV3, Soonsimhwan, Hanpoong Pharm, Korea). Bojungikgi-tang (CV1) will be administered one sachet (3.75 g) twice a day before or in between meals. Kyungok-go (CV2) will be administered one sachet (20 g) twice a day in the morning and evening before or in between meals. Cheonwangbosim-dan (CV3) will be administered one sachet (one dose) once a day in between meals. The evaluation for the continuation of herbal medicine administration will be conducted at visits 2 and 3. If visual analog scale (VAS, 0–100) for fatigue or cognitive dysfunction at the current visit is improved by <50% of VAS at the previous visit, and the patients want to take herbal medicine, the same herbal medicine as previously prescribed will be re-administered for 4 weeks. For this evaluation, the symptom improvement rate at the current visit (VAS score of the current visit/VAS score of the previous visit (%)) and whether the patients want to continue the administration of herbal medicines will be investigated.

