### 2.8. Outcomes

#### 2.8.1. Primary Outcome

As the primary outcome, the treatment success rate after herbal medications for up to 12 weeks for fatigue and cognitive dysfunction in patients who have recovered from COVID-19 will be evaluated. VAS (0–100) for fatigue or cognitive dysfunction before (visit 1) and after administration of herbal medicines (visit 4) will be assessed. If VAS is >15 points, it is defined as treatment success. The frequency or ratio of treatment success patients will be presented, based on the fatigue and cognitive dysfunction groups, respectively.

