#### 2.8.2. Secondary Outcome

##### Medication Adherence

Medication adherence will be monitored by counting the number of returned and taken medications at each visit. In the case of the number of returned drugs and number of taken drugs being unmatched with the number of prescribed drugs, the reason for this shall be recorded in the case report form. Medication adherence is calculated as follows:$$Medication\;adherence\;\left(\%\right)=\frac{The\;number\;of\;taken\;drugs}{The\;number\;of\;prescribed\;drugs\;in\;the\;duration\;*}\times 100$$
* The number of prescribed drugs in the duration means the number of drugs should be taken from the time of initial administration to before the time of returning the untaken drugs.

The final medication adherence will be evaluated at 12 weeks after the initial administration (visit 4 or end point of medication), and the sum of the number of taken herbal medicines divided by the sum of the number of prescribed herbal medicines in the duration will be calculated and collected at visits 2, 3, and 4. Mean, standard deviation, median, minimum, and maximum value of the final medication adherences (%) for all study patients will be represented for each herbal medicine group, and multiple comparison analyses will be conducted among groups.

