##### Analysis of Patient Recruitment Rate, Enrolment Rate, Dropout Rate, and Reasons for Dropout for Feasibility Evaluation

The patient recruitment rate is calculated by the ratio (total, each intervention group) of recruited patients during the study period to planned study patients (45 patients, 15 patients per each intervention group). The patient enrolment rate is calculated by dividing the total number of study patients by the total number of screening patients. Reasons for dropout will be documented, and the dropout rate is calculated and will be compared for all study patients and each intervention group.

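### Section 2.4.3 merges reasons to stop the medicine with reasons to end observation, so the visit 4 VAS is not secured for patients who stop for poor tolerance

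*Protocol article*

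**What the plan says.** Section 2.4.3 opens with "The reasons for withdrawal and discontinuing herbal medication or observation shall be documented". One list follows, labelled as the criteria for withdrawing patients. Its first item is "Acute reaction (allergy, hypersensitivity, and others) to herbal medicine". A later item is "No longer possible to administer or make observations due to severe adverse events or adverse drug reaction", and a parallel item applies the same wording to unexpected illness or accident. Withdrawal of consent is in the same list.

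The primary outcome (section 2.8.1) is the treatment success rate, based on the VAS "before (visit 1) and after administration of herbal medicines (visit 4) will be assessed". It is reported separately for the fatigue and cognitive dysfunction groups.

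Other places that bear on the point:

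- Section 2.7 re-prescribes at visits 2 and 3 only if the VAS "is improved by <50% of VAS at the previous visit, and the patients want to take herbal medicine". A patient who has improved more than that is simply not re-prescribed.
- The Medication Adherence paragraph evaluates final adherence at "visit 4 or end point of medication".
- Sections 2.10 and 2.10.2 record the course and resolution of adverse events and follow significant abnormal tests until improvement.
- Table 1 schedules the VAS at visits 2 to 6 and also at an unscheduled visit.
- In the feasibility evaluation, "Reasons for dropout will be documented, and the dropout rate is calculated".
- Section 2.3 says "The results from this study will be used to calculate the sample size for further confirmatory clinical trials".

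**The concern.** Stopping a medicine and leaving a trial are different events. A patient with an allergic reaction to a herbal product should stop taking it, but can usually still mark a VAS at week 13. The list in section 2.4.3 gives both events the same consequence: the patient is withdrawn.

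The patients affected are those who tolerate the medicine poorly, and there is no reason to assume that their outcomes match those of the others. The trial has no control group (section 2.6), so each symptom group's success rate is itself the primary result, and the results are meant to feed the sample size of a confirmatory trial. An analysis plan can say how a missing value is handled, but it cannot recover a VAS that was never collected. Reported dropout counts and reasons would make the loss visible without supplying the outcomes.

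**Working it through.** The plan has no figure of its own to reproduce here: section 2.3 sets 45 patients without a calculation (3 × 15 = 45). The check is first one of wording, then of scale.

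**Wording**

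1. Acute reaction stands alone in the list. No condition says that the patient must also be impossible to assess.
2. In the adverse-event item, administering and observing are joined by *or*. Inability to give the medicine therefore meets the criterion even when observation remains possible.
3. The lead sentence of section 2.4.3 names medication and observation as two things that may be discontinued, but the list assigns no criterion to one rather than the other.
4. The remaining places do not close the gap. The adherence paragraph foresees medicine ending before visit 4, but only for counting doses. Sections 2.10 and 2.10.2 concern safety. The unscheduled visit in Table 1 includes a VAS, but nothing says that withdrawal triggers the visit, and it need not fall at week 13.
5. For patients who stop because they improved, no withdrawal criterion applies, so the Table 1 schedule stands for them. The design thus already allows for assessing patients off medicine.

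**Scale**

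Inputs: 15 patients per herbal group (section 2.3); the fatigue group combines two herbal groups, so n = 30, and the cognitive dysfunction group has n = 15 (section 2.7).

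If m patients lack a visit 4 VAS and their outcome is not fixed by definition, the rate among all n can lie anywhere in a range of width m/n.

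| Missing VAS | Cognitive dysfunction (n = 15) | Fatigue (n = 30) |
|---|---|---|
| 1 | 1/15 = 6.7 points | 1/30 = 3.3 points |
| 2 | 2/15 = 13.3 points | 2/30 = 6.7 points |

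Example: 8 successes among 13 observed, two missing, gives between 8/15 = 53.3% and 10/15 = 66.7%. With 16 among 28, the range is 16/30 = 53.3% to 18/30 = 60.0%.

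**Direction**

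The success rates and the number of leavers below are assumptions, not document figures. Assume two leavers and true rates, counting the week 13 VAS whether or not the medicine was stopped, of 8/15 and 16/30 (both 53.3%).

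| Handling and true outcome of the two leavers | Cognitive dysfunction | Fatigue |
|---|---|---|
| Left out; both non-successes | 8/13 = 61.5% (+8.2) | 16/28 = 57.1% (+3.8) |
| Left out; one a success | 7/13 = 53.8% (+0.5) | 15/28 = 53.6% (+0.2) |
| Counted as non-successes; truly so | 8/15 = 53.3% (0) | 16/30 = 53.3% (0) |
| Counted as non-successes; one truly a success | 7/15 = 46.7% (−6.7) | 15/30 = 50.0% (−3.3) |

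The difference can be positive, nil or negative. For comparison, the exact (Clopper-Pearson) 95% interval for 8/15 is 26.6% to 78.7%.

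**The case against.** The strongest reply is that section 2.4.3 lists reasons and is silent on what is assessed afterwards. Procedures after discontinuation are commonly left to the full protocol, which is not shown and may separate the two events. The heading and lead sentence name both kinds of stopping, and Table 1 schedules the VAS with no exception for anyone. Sections 2.10 and 2.10.2 show that a reaction does not end all contact. This stands in part: the wording is open to a second reading. It does not remove the point, because the article prints the rule that decides who is withdrawn, and as printed that rule merges the two events.

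A second reply is that a responder endpoint may define stopping for intolerance as non-success. The outcome is then known and nothing is left open. This stands in full, and the ranges above apply only where that definition is not used. The negative differences likewise presuppose a target of the week 13 VAS regardless of stopping, which the article does not fix.

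A third reply is that the effect lies within sampling error in a preliminary trial of 45 patients, with no test or threshold set for the primary rate and dropout reported by group. That limits the weight of the point. Sampling error is unavoidable at this size, however, whereas this loss is avoidable.

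A reader might infer that the plan orders assessments to stop after a reaction, or that the reported success rate will be too high. The article says neither. It does not forbid a VAS after withdrawal, and the rate is too high only if such patients are left out and succeed less often than the rest.

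**Conclusion.** The point holds as a cheap improvement to a conduct rule. Followed as written, section 2.4.3 withdraws patients who stop for poor tolerance but could still be assessed, and nothing shown secures their visit 4 VAS. Unless intolerance is defined as non-success, one such patient leaves up to 6.7 points of the cognitive dysfunction rate or 3.3 points of the fatigue rate undetermined. This rests on the planned group sizes of 15 and 30 and on the ordinary reading that a withdrawn patient leaves the trial. How many patients would be affected, and in which direction any bias would run, cannot be derived from the article. Confidence is medium: the merged list is plain, but the full protocol could resolve it.

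**What to change.** State in section 2.4.3 that an acute reaction, or inability to administer the medicine because of illness, accident or adverse events, ends the medicine only. Add that scheduled VAS and safety assessments then continue to at least visit 4 (week 13) unless consent is withdrawn or observation is impossible. The reasons for stopping the medicine stay as they are, so no safeguard is lost.

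The cost is a wording change and a few already scheduled visits attended off medicine. The success rate will then include patients with partial courses and may be lower. In return, patients who reacted also keep their scheduled safety assessments, which serves the trial's safety aim.
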